**Figure 1 F1:**
[figure not shown]
Present the technology roadmap.

**Table 1 T1:** Clinical observation flow charts.

Research stage	Selection period	Treatment period		Follow-up period
Evaluation times	First time	Second	Third time	Fourth
Evaluation time point	1 and 0 days before treatment	1 week after intervention	2 weeks after intervention	1 month after the end of the intervention
Inclusion criteria	•			
Exclusion criteria	•			
Informed consent form	•			
Online random grouping	•			
General assessment				
General information	•			
Current medical history/allergic history	•			
Past history/complications	•			
Evaluation of the curative effect index				
VFSS	•		•	
SSA	•	•	•	•
Surface electromyography signal	•	•	•	
Improved Barthel index	•	•	•	
SS-QOL				•
Security assessment				
Life indication	•	•	•	•
Other assessments				
Adverse reactions/events		•	•	
Recurrence situation				•
Treatment compliance			•	

SSA = standardized swallowing assessment, SS-QOL = stroke-specific quality of life scale, VFSS = videofluoroscopic swallowing examination.

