#### Source and distribution of research objects

2.9.1

The patients will be randomly divided into the experimental and control groups (both n = 126). Eighty-four cases will be obtained in the Second Affiliated Hospital of Heilongjiang University of Traditional Chinese Medicine, Changchun University of Chinese Medicine, and China Rehabilitation Research Center.

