### Sample size calculation

2.16

Referring to Liu Zhishun's “clinical study on acupuncture treatment of chronic moderate and severe dysphagia in stroke,” the effective rate of traditional rehabilitation is 80%, the estimated effective rate is 93.3%. According to the preset parameters, the effectiveness of the two groups were calculated with PASS 8.0 software, and 97 samples were needed for each group. At the same time, abscission and elimination were considered. The abscission rate was 30% and each group needed 126 samples. Therefore, 252 subjects were expected to be included in this study.

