### Statistical analysis

2.17

A third-party medical statistics professional (Guangdong Provincial Hospital of Traditional Chinese Medicine) will perform statistical analysis. After the subject research plan and case report form are reviewed by experts, a third party will formulate a statistical analysis plan and determine the statistical software to use.

1.Full Analysis Data Set (FAS): A total of 252 random numbers were designed in this study to exclude subjects in a minimum and reasonable manner according to the principle of intentionality analysis. This data set includes all subjects receiving treatment. Missing data for key indicators are carried forward to the closest observation (LOCF).2.Per-Protocol Data Set: those who have good compliance (who have received at least 2/3 or more of the courses of treatment), whose main indicators of observation are not missing, who have basically not violated the Protocol, and who meet the inclusion criteria without any exclusion indicator constitute the current PP population. Missing data in this data set is not carried forward, but is treated as missing data.

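### The 30% allowance in section 2.16 corrects only the head count, while the full analysis set in 2.17 keeps treated drop-outs, so the 13.3-point difference can shrink there, to about 9.3 points in the least favourable case considered

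*Protocol article*

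**What the plan says.** Section 2.16 takes its rates from a cited study: "the effective rate of traditional rehabilitation is 80%, the estimated effective rate is 93.3"%. It does not give the significance level, the sidedness or the power, only "According to the preset parameters". The result is that "97 samples were needed for each group". The allowance follows: "At the same time, abscission and elimination were considered", and then "The abscission rate was 30% and each group needed 126 samples". Section 2.9.1 confirms 126 in each arm.

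Section 2.17 defines the full analysis set on the intention-to-treat principle: "This data set includes all subjects receiving treatment". Missing key indicators are filled by LOCF. Section 2.7 likewise keeps discontinued patients in the efficacy analysis with their last result.

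Table 1, under "Evaluation of the curative effect index", schedules VFSS at baseline and week 2 only. SSA is scheduled at baseline, week 1, week 2 and follow-up. Sections 2.2 and 2.10.1 both name SSA and VFSS as primary.

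Other passages point elsewhere. Section 2.8 lists withdrawals and patients with insufficient data as case exclusions. Section 2.6 appears to count drop-outs in the efficacy statistics only after more than one treatment course.

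**The concern.** Adding patients to replace losses makes sense when the lost patients are not analysed: the remaining patients carry the assumed difference and only their number needs protecting. In a set that retains drop-outs, the number is already protected. What is at risk is the difference, because patients who left early may show less of it, and nothing in section 2.16 allows for that.

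The two named primary outcomes differ here. A treated patient who misses the week-2 VFSS has only a baseline value to carry forward, so enters as unchanged, and hence not effective, in either arm. For SSA, LOCF can carry a week-1 value that may hold part of the effect.

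At stake is how the result is read. If 126 per group is taken as covering the intention-to-treat comparison when it may not, a null result there could be misread as absence of benefit. Weight could then shift to the per-protocol set, which drops randomised patients.

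**Working it through.** **Inputs.** From 2.16: p1 = 0.80, p2 = 0.933, 97 per group, 30% loss, 126 per group. From 2.17: treated drop-outs retained, LOCF. Assumed, because the article does not state them: two-sided 5% test, 80% power, equal loss in the two arms, all 30% remaining in the full analysis set.

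**Step 1: reproduce 97.** Arcsine formula: n = 2(1.960 + 0.842)² / h², with h = 2·asin(√0.933) − 2·asin(√0.80) = 2.618 − 2.214 = 0.404. This gives n = 96.3, rounded up to 97. Other two-sided formulas come close (unpooled normal 98.7, pooled 102), and a one-sided test with continuity correction gives 95. The assumed parameters are therefore plausible but not proven. The exact power of the uncorrected chi-square test at 97 per group, 80% versus 93.3%, is 80%.

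**Step 2: reproduce 126.** 97 × 1.3 = 126.1. With 30% loss, 126 × 0.7 = 88.2, so about 88 patients per group have complete data, not 97. (97 / 0.7 = 138.6, or 139, is a separate point.)

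**Step 3: dilution with no difference among drop-outs.** If drop-outs are effective at the same rate d in both arms, the full-analysis rates are 0.7 × 0.80 + 0.3d and 0.7 × 0.933 + 0.3d. The difference is 0.7 × 13.3 = 9.31 points whatever d is. Exact chi-square power at 126 per group:

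| d | Control | Experimental | Power |
|---|---|---|---|
| 0% | 56.0% | 65.3% | 32% |
| 50% | 71.0% | 80.3% | 41% |
| 80% | 80.0% | 89.3% | 54% |
| 100% | 86.0% | 95.3% | 74% |

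The first row is what LOCF produces for VFSS when week 2 is missing.

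**Step 4: drop-outs keep a fraction g of the difference.** The difference becomes 13.3 × (0.7 + 0.3g) points.

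| g | Control drop-outs effective | Difference (points) | Rates compared | Power at 126 |
|---|---|---|---|---|
| 0.5 | 50% | 11.3 | 71.0% vs 82.3% | 57% |
| 0.5 | 80% | 11.3 | 80.0% vs 91.3% | 73% |
| 0.7 | 80% | 12.1 | 80.0% vs 92.1% | about 80% |
| 1 | 80% | 13.3 | 80.0% vs 93.3% | 89% |

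**Step 5: other test assumptions.** With a one-sided test and the pooled normal formula, power at 126 with no difference among drop-outs runs from 45% to 82%, against 86% at 97 with the full difference. The level moves, but the shortfall remains.

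**The case against.** A reader might infer that the difference in the full analysis set will be 9.3 points and that the trial is plainly underpowered there. The document does not support this, for five reasons.

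- **No stated drop-out rates.** The 9.3 points needs all 30% to stay in the set with zero difference between groups. The article gives no effective rate for drop-outs.
- **What the 30% covers.** It includes eliminations, and sections 2.6 and 2.8 may remove some of these patients from the analysis.
- **Which outcome.** Section 2.16 does not tie its effective rate to VFSS, so the 32% figure cannot be presented as the power of the trial. SSA has a week-1 value, and section 2.6 asks staff to contact drop-outs and evaluate them, so some may contribute a real measurement.
- **Source of the rates.** If 80% and 93.3% already include drop-outs, 126 per group gives 89% power at the full difference, which is ample. The cited study is not available to settle this.
- **Unstated parameters.** The power behind 97 is inferred.

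Each of these stands as a limit on size. None removes the mismatch: the allowance treats patients as leaving, the full analysis set keeps those who were treated, and the article does not say which patients the rates describe. It might also be said that naming the deciding analysis set belongs in the analysis plan. That is fair, and it is not asked for here. The effect size, the allowance, the full analysis set and LOCF are all fixed in this article.

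**Conclusion.** The point holds in conditional form. The sample size protects the count but not the difference in the set that retains drop-outs. If the 30% stay in with no difference between groups, power is below the 80% attributed to 97 at every drop-out rate examined. This is the expected case for VFSS, and less so for SSA. If control drop-outs are 80% effective, power returns to about 80% once drop-outs keep about 70% of the difference.

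These figures rest on a two-sided 5% chi-square test, 30% loss in each arm, all of it retained, and 80% and 93.3% being completer rates. Correcting the inflation to 139 per group would not resolve the matter: with drop-outs all counted as not effective, power would be about 36%.

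**What to change.** In section 2.16:

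- State that 97 per group refers to patients with complete data, and that 126 with 30% loss leaves about 88.
- Say whether 80% and 93.3% are rates among completers or among all treated patients.
- State the significance level, sidedness and power used.
- Report the power of the full analysis set at 126 per group over the whole range above, from no retained difference to full retention, with the assumptions beside each figure. Quoting only the low end would mislead as much as quoting only the 80%.

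Reconcile sections 2.6, 2.7, 2.8 and 2.17 on whether patients who withdraw after starting treatment stay in the full analysis set, so that the restated power belongs to a defined population.

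The cost is a few sentences and a less favourable power statement. No extra patients are asked for.

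### The 30% drop-out allowance was added to 97 instead of divided out, so at that loss 126 per group leaves about 88 patients with observed outcomes, not 97

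*Protocol article*

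**What the plan says.** Section 2.16 (Sample size calculation) assumes effective rates of 80% for conventional rehabilitation and 93.3% for the comparison. It reports the software result that "97 samples were needed for each group". It then turns to losses: "At the same time, abscission and elimination were considered". The next sentence gives the rate and the result: "The abscission rate was 30% and each group needed 126 samples". The total follows: "Therefore, 252 subjects were expected to be included in this study".

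Section 2.9.1 repeats 126 per group, and the abstract and section 2.17 carry the total of 252. The article prints no inflation formula. Significance level, sidedness, power and test are covered only by a reference to preset parameters.

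Three other sections bear on what happens to patients who are lost:

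- Section 2.17 puts all treated subjects in the full analysis set and carries the last observation forward for key indicators. Its per-protocol set requires main indicators that are not missing, and carries nothing forward.
- Section 2.7 takes the last result of a discontinued patient as the final one and includes it in the efficacy analysis.
- Section 2.8 lists cases to be excluded, among them patients who withdraw or have insufficient data.

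**The concern.** An allowance for losses has one purpose: the required number should still be there once the expected losses have occurred. The enrolled number must therefore be the required number divided by the share expected to remain. Here 30% of the required number was added instead, which applies the rate to the wrong base. At 5% the two methods differ by one patient per group (102 against 103). At 30% they differ by 13.

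At stake is the statement that 252 patients cover a 30% loss. A reader will conclude that 97 patients per group with observed outcomes are secured at that rate. They are secured only at a lower one. The sentence is also the only justification that the article gives for going from 97 to 126.

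**Working it through.** **Inputs, all from section 2.16:** required number 97 per group; drop-out rate 30%; enrolled number 126 per group, 252 in total; effective rates 80% and 93.3%.

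**1. Reproducing the plan's figure**

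- Added on: 97 × (1 + 0.30) = 126.1, which gives the stated 126.
- Divided out: 97 / (1 − 0.30) = 138.6, rounded up to 139. This does not give 126.

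The stated figure therefore comes from the first formula.

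**2. What 126 delivers at the plan's own rate**

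- Remaining per group: 126 × 0.70 = 88.2, about 88.
- Shortfall: 97 − 88 = 9 per group, 18 in total.
- Largest loss that still leaves 97: 1 − 97/126 = 23.0%.

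**3. What protecting 97 at 30% would take**

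- 139 per group, 278 in total: 13 more per group and 26 more in total than planned.

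Steps 1 to 3 do not depend on significance level, power or test.

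**4. Effect on power (conditional)**

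The article does not state its design parameters, so I assume two-sided 5% and 80% power. This is plausible, because two methods then return 97: the arcsine formula gives 96.3, rounded up to 97, and with an exactly enumerated chi-square test 97 is the first size to reach 80% (79.6% at 96, 80.1% at 97). It is not proof, since other common formulas give 99 (unpooled normal) or 102 (pooled normal) under the same assumption.

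Power for 80% against 93.3%, two-sided 5%:

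| Method | 97 per group | 88 per group | 126 per group |
|---|---|---|---|
| Chi-square, exact enumeration | 80.1% | 75.8% | 89.0% |
| Arcsine | 80.3% | 76.3% | 89.3% |
| Unpooled normal | 79.3% | 75.3% | 88.6% |
| Pooled normal | 78.2% | 74.1% | 87.8% |

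Whatever the method, going from 97 to 88 costs about 4 percentage points.

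**The case against.** The strongest reply is that most patients who drop out are not lost to the main analysis. Under sections 2.17 and 2.7 treated patients stay in the full analysis set with their last value, so that set approaches 126 per group, where nominal power is 88% to 89%. This stands, and it limits the point. A reader might infer that the trial as a whole misses its target and is underpowered. The documents do not support that: the 88 describes completers and the per-protocol set, not the full analysis set.

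The reply does not rescue the sentence in 2.16. The allowance is said there to cover both drop-out and elimination, so its aim is to have 97 left after losses. Section 2.8 removes withdrawn patients and those with insufficient data, and the per-protocol set carries nothing forward. A carried-forward value also does not supply the observed outcome that the allowance was meant to secure.

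A second reply is that no formula is printed. If 30% is read as a mark-up on 97, then 97, 30% and 126 agree. So it would go too far to say that the three figures cannot be reconciled under any reading. But the text calls the 30% a drop-out rate, and the ordinary meaning of that is a share of those enrolled.

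A third reply is that the power figures rest on parameters that the article does not give. That is right, and they are offered only conditionally. An article may leave those parameters to the full protocol, so their absence is not part of this point.

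**Conclusion.** The drop-out step in section 2.16 is wrong as written. At the plan's own 30% loss, 126 per group leaves about 88 patients with complete observed data, 9 short of the stated 97, and 97 is preserved only up to a 23% loss. This rests on the printed figures and on reading the drop-out rate as a share of those enrolled.

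The 88 further assumes that the 30% covers all losses, elimination included. If the preset parameters are two-sided 5% and 80% power, power among completers falls from about 80% to about 76% (74% to 76% by method).

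The size is modest. It touches observed outcomes and the per-protocol set; neither the test nor the headcount of the full analysis set changes materially. It is a correction that should be made, and it does not by itself show that more patients are needed.

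**What to change.** Keep 252 patients and the 30% expectation, and restate section 2.16 to say that:

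- 126 per group leaves about 88 completers per group at a 30% loss;
- 97 completers per group are preserved only up to a 23% loss;
- power at 88 per group is the value obtained from the sponsor's own preset parameters, given beside them. Under two-sided 5% and 80% power for 80% against 93.3%, that would be about 76%.

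Replacing 30% by 23% alone would not do. It would derive the expected loss from the chosen sample size, and nothing in the article supports 23% as an expectation. The 23% belongs in the text only as a limit, next to the 30% and the resulting shortfall.

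The restatement costs a sentence or two and a slightly less favourable power figure, with no extra patients. Only if the sponsor wants 97 completers per group protected at a 30% loss would the number become 139 per group, 278 in total. That means 26 more patients, and sections 2.9.1 and 2.17 and the abstract would have to be brought into line.

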### Statistical analysis

2.17

A third-party medical statistics professional (Guangdong Provincial Hospital of Traditional Chinese Medicine) will perform statistical analysis. After the subject research plan and case report form are reviewed by experts, a third party will formulate a statistical analysis plan and determine the statistical software to use.

1.Full Analysis Data Set (FAS): A total of 252 random numbers were designed in this study to exclude subjects in a minimum and reasonable manner according to the principle of intentionality analysis. This data set includes all subjects receiving treatment. Missing data for key indicators are carried forward to the closest observation (LOCF).2.Per-Protocol Data Set: those who have good compliance (who have received at least 2/3 or more of the courses of treatment), whose main indicators of observation are not missing, who have basically not violated the Protocol, and who meet the inclusion criteria without any exclusion indicator constitute the current PP population. Missing data in this data set is not carried forward, but is treated as missing data.

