### Study design

2.2

This will be a multicenter, randomized controlled study conducted at the Second Affiliated Hospital of Heilongjiang University of Traditional Chinese Medicine, Changchun University of Traditional Chinese Medicine, and China Rehabilitation Research Center from December 1, 2018, to December 31, 2021. Patients with post-stroke dysphagia who meet the inclusion criteria will be divided into the experimental and control groups using a central randomization system. The experimental and control groups will receive acupuncture treatment and conventional rehabilitation training, respectively. The primary results will be obtained using the standardized swallowing assessment (SSA), videofluoroscopic swallowing study (VFSS), and fMRI. The secondary observation indicators will include surface electromyography (sEMG) analysis and modified Barthel index (MBI). The follow-up indicators include stroke-specific quality of life scale (SS-QOL) and the SSA. Measurements will be obtained before treatment, as well as 1 week, 2 weeks, and 1 month after treatment. fMRI will be only performed in the subject unit. Forty-two participants will undergo pre- and post-treatment fMRI assessment to analyze the central regulatory mechanism underlying swallowing function remodeling in the rehabilitation program of TCM. Figure 1 and Table 1 present the technology roadmap and clinical observation flow charts, respectively.

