### Randomization and allocation concealment

2.14

The main researchers of each unit will be assigned different user names and passwords to establish a central random system and data collection system. Before treatment, the patient information will be entered into the central random system; moreover, the patient will be screened according to the inclusion and exclusion criteria. Patients who meet the criteria will be randomly divided into the control and experimental groups.

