### Blinding

2.15

In this study, due to the specificity of clinical acupuncture research, it is difficult to implement blind method. But it can be assessed by people who are not involved. We plan to assign specialized doctors from rehab centers as reviewers, and they will not be told how the subjects are grouped.

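### The full analysis set is limited to patients who receive treatment, although patients know their arm and allocation comes first, so refusal that depends on the arm can remove randomised patients from a set built on the intention-to-treat principle

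*Protocol article*

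**What the plan says.** Section 2.17 (Statistical analysis) introduces the FAS with the planned number of randomisations, "A total of 252 random numbers were designed in this study", and says the aim is "to exclude subjects in a minimum and reasonable manner according to the principle of intentionality analysis". The translation is rough, but this is plainly the intention-to-treat principle. The next sentence sets membership: "This data set includes all subjects receiving treatment". Missing key outcomes in the FAS are filled by last observation carried forward (LOCF).

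Four other places bear on this:

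- **Timing.** Section 2.14: "Before treatment, the patient information will be entered into the central random system". Table 1 puts online randomisation at the first visit, 1 to 0 days before treatment.
- **Contrast.** Section 2.2: "The experimental and control groups will receive acupuncture treatment and conventional rehabilitation training, respectively". No sham is described.
- **Blinding.** Section 2.15: "due to the specificity of clinical acupuncture research, it is difficult to implement blind method". Only the assessors are masked: "they will not be told how the subjects are grouped".
- **Exclusions.** Section 2.8 removes patients placed in the wrong group, those who withdraw and those with insufficient data. It does not say which analysis set this governs.

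No section defines a set of all randomised patients or returns never-treated patients to the FAS.

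**The concern.** Leaving never-treated patients out of an FAS is usually defensible when the decision to start cannot depend on the assigned arm, as in a double-blind trial. That condition is not secured here. One arm receives needling of the neck, face, throat and tongue; the other receives oral and breathing exercises. A patient may decline the needling, or may decline the exercises because acupuncture was hoped for. Either refusal is an event after randomisation that the arm can influence.

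If refusers differ in prognosis from those who start, and refusal differs between arms, the FAS no longer compares the groups as randomised. The difference can be pushed either way. Masked assessors protect the rating of outcomes, but they have no bearing on who enters the data set.

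Section 2.8 adds to the problem. If its exclusions were applied to the FAS, withdrawn and wrongly grouped patients would be removed as well.

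**Working it through.** **The plan's own figures.** The documents give no never-treated rate, so there is no stated figure for this point to reproduce. The sample size supplies the 80% response used below. With 80% against 93.3%, and an assumed two-sided 5% level and 80% power, the arcsine formula gives 96.3, rounded up to the stated 97 per group. Then 97 × 1.3 = 126.1, the stated 126. The point does not rest on these numbers, and the fix does not change them.

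**Who leaves the FAS.** Reading the sections in order:

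1. The patient is entered and allocated before treatment (2.14; Table 1).
2. The patient can tell acupuncture from exercises (2.2, 2.15).
3. The patient may withdraw voluntarily (2.6).
4. If this happens before the first session, the patient is one of the 252 randomised but has received no treatment, and so falls outside the FAS as defined.

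**Illustration of size.** Inputs:

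- p = 0.80, response in each arm as randomised, with no true effect (control rate from 2.16)
- n = 126 per arm (2.9.1)
- f = fraction of one arm that never starts (assumed 5% to 10%, or about 6 to 13 patients)
- r = response those patients would have had (assumed)

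Rate among those kept in the arm = (p − f × r) / (1 − f). The type I error is a normal approximation, two-sided at 5%, with losses in one arm only.

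| f | r | Rate kept | Shift | Type I error |
|---|---|---|---|---|
| 5% | 60% | (0.80 − 0.030)/0.95 = 81.1% | +1.1 points | 5.5% |
| 10% | 60% | (0.80 − 0.060)/0.90 = 82.2% | +2.2 points | 7.2% |
| 5% | 70% | (0.80 − 0.035)/0.95 = 80.5% | +0.5 points | 5.1% |
| 10% | 70% | (0.80 − 0.070)/0.90 = 81.1% | +1.1 points | 5.5% |

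The planned difference is 93.3 − 80 = 13.3 points, so a shift of 2.2 points is about one sixth of it (2.2/13.3 = 0.17). The shift favours whichever arm loses the patients. Similar refusal in both arms largely cancels.

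**What happens if never-treated patients are added but LOCF is kept.** A patient with baseline data only would have baseline carried forward and, if scored as not effective, would count as a failure. With f = 10% and r = 60%, the arm's rate becomes 0.90 × 82.2% = 74%. That is 6 points below the true 80%, a larger error than the +2.2 being removed. Redefining the set without changing the missing-data rule can therefore make matters worse.

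**The case against.** The strongest reply has four parts.

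**The window is short.** Table 1 allows at most about one day between allocation and treatment, possibly none, and no section says when patients learn their arm. Section 2.11 has patients told of benefits and risks before enrolment, so some who dislike needling would decline before randomisation. This stands: never-starting is likely to be uncommon.

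**The wording is loose.** The sentence says the set includes all treated subjects, not only those, and the principle as stated, "exclude subjects in a minimum and reasonable manner according to the principle of intentionality analysis", openly allows some exclusions. A restrictive reading is still the natural one, because the sentence gives the only membership condition. Minimal exclusion is not secured by a condition that the known arm can influence.

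**The FAS is not named as the main analysis.** A reader might infer that the trial's main analysis is biased. The documents do not support that: 2.17 defines an FAS and a per-protocol set, names neither as primary, and leaves the analysis plan to a third party. The point concerns how the FAS is defined.

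**Analysis as allocated is usually left to the SAP.** A reader might treat its absence from 2.17 as a separate fault. It is not one; the wording belongs in the fix only because the membership sentence has to be rewritten anyway.

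**Conclusion.** The point holds as a defect in the FAS definition. Section 2.17 states the intention-to-treat principle and then sets a membership rule that permits arm-dependent exclusion after randomisation. It is not a matter simply deferred to the SAP, because the membership rule is already stated and an SAP that followed it would inherit the problem.

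The direction is open and the size unknown. Under the stated assumptions (no true effect, 80% response overall, 60% in refusers, 5% to 10% lost from one arm only) the shift is +1.1 to +2.2 points. Given the short window it is probably small, and it is smaller still if refusers resemble the rest or refuse equally in both arms.

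A reader might infer a bias as large as one third of the planned difference. That needs 10% lost from one arm only and a 40% response in those lost: (0.80 − 0.040)/0.90 = 84.4%, or +4.4 of 13.3 points. This is an extreme corner of assumed values, and nothing in the documents suggests it.

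**What to change.** - **2.17, membership.** Define the FAS as all randomised patients, analysed in the arm allocated by the central system. Exclude only patients found ineligible from data recorded before randomisation, judged without knowledge of arm. Keep all-treated as a sensitivity set.
- **2.17, missing data.** Do not fill the outcomes of never-treated patients by carrying baseline forward. State a missing-data method for them, with a sensitivity analysis.
- **Follow-up.** Seek the scheduled week-2 and 1-month assessments from never-treated patients, using the contact with drop-outs that 2.6 already requires.
- **2.8.** State that the exclusions for wrong group, withdrawal and insufficient data apply to the per-protocol set and not to the FAS.

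The cost is a few sentences in 2.17 and 2.8, matching text in the SAP, and some follow-up effort. The sample size does not change. A few patients with baseline data only will need missing-data handling, and the estimate may be slightly diluted.
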